#### Primary efficacy analysis

The primary outcome measure is d_3_mft at two years of follow up compared to the d3mft at baseline (d_3_mft is dental decay as measured by the number of: teeth affected by decay into the dentine; missing teeth; and filled teeth). The primary analysis is the comparison between the treatment groups in percentages of children experiencing new decay as defined by the primary endpoint, namely an increase in d_3_mft.

#### Secondary efficacy analysis

Secondary analyses will be of:absolute change in d_3_mft at 2 years of follow up minus the d_3_mft at baseline,absolute change in d_3_mfs at 2 years of follow up minus the d_3_mfs at baseline.

We will do pre-defined subgroup analyses on the following types of subgroup:children with pre-existing disease, children without pre-existing disease,we will attempt to split the children into areas that are ‘extremely’ deprived and only ‘very deprived’ based on the SIMD of the child’s postcode.

#### Safety analysis

The safety data (adverse reactions) – both numbers of subjects and reactions – will be summarised by randomised group and overall using descriptive statistics. No formal statistical tests comparing the randomised groups will be pre-specified.

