#### Visit 1/visit 2: Examination/randomisation/0 month intervention visit(s)

At this visit study staff will confirm eligibility before the baseline dental examination is carried out by a study dental practitioner (e.g., signed consent form is in place, enquiry form regarding contraindications is complete and the child has no obvious temporary infections or injuries which would lead to exclusion on the day). Completion of CRF containing dental examination data.

All children receive treatment as usual (TAU), namely supervised toothbrushing in the nursery. Randomisation will take place via a telephone call to the IRVS at the Robertson Centre for Biostatistics. As soon as possible following randomisation, the study Childsmile team will perform a brief oral check, depending on randomisation they either get a “sham” fluoride varnish application (applicator brushing teeth with no fluoride varnish on it) or they get the active treatment involving application of fluoride varnish. The dental nurse will record treatment arm in order to ensure consistency of treatment throughout the sequence of visits.

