##### Adverse Reaction (AR)

Any untoward and unintended response in a subject to an investigational medicinal product which is related to any dose administered to that subject.

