#### Detection, recording and reporting of Adverse Events

It is not proposed to collect details of all adverse events occurring in this study. Only information on adverse reactions to the IMP will be collected. The applications are spaced approximately 6 months apart, and it is inappropriate and unnecessary to attempt to collect information throughout each 6 month period on events unrelated to the varnish application, when it is known what the very specific, immediate and limited range of possible adverse reactions may be. Any adverse reaction is extremely likely to be seen within a maximum of 24 h post application. Any adverse events reported by parents during that time will be recorded and evaluated by the Childsmile coordinator and the local Principal Investigator irrespective of whether it constitutes a possible reaction or an unconnected event.

All Adverse reactions must be recorded, notified, assessed, reported, analysed and managed in accordance with the Medicines for Human Use (Clinical Trials) Regulations 2004 (as amended) and this protocol. (See Safety Flow chart- Additional file 8).

Any adverse reactions to the fluoride varnish (e.g., mucositis, allergy etc.), whether noted by Childsmile staff or reported to Childsmile staff by parents or the nursery school, will cause either the study dental nurse or dental health support worker to record details in the Case Report Form and to inform the site Principal Investigator to review such events. The parents or guardian may refer to the fluoride varnish aftercare leaflet for details of the local Childsmile Coordinators acting as the contact point regarding any possible adverse reaction.

The site Principal Investigator will assess the severity and seriousness of such events, and re-assess their relatedness to the administration of Duraphat varnish. Events deemed to be serious and related to the administration of the varnish will be classified as serious adverse reactions (SARs). SARs are to be reported by the site to the Sponsor’s Pharmacovigilance Office within 24 h of awareness of such event for assessment against the criteria of expectedness. The management of SARs is detailed below.

The expectedness of an adverse reaction is assessed against the approved Reference Safety Information i.e., the list of expected reactions detailed in the SmPC.

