#### Severity

This should be assessed and described using the following categories:mild-awareness of event but easily tolerated,moderate-discomfort enough to cause some interference with usual activity,severe-inability to carry out usual activity.

Any AE that is assessed as serious, is suspected of having a causal relationship to the trial medication and is unexpected is a SUSAR and will require expedited reporting to the MHRA/Ethics Committee as detailed below. Should an SAR be deemed to be unexpected, the Pharmacovigilance Office will liaise with the Chief Investigator to complete the expedited safety report.

Adverse reactions and Serious Adverse Reactions that occur up to 24 h after Fluoride varnish application will be reported.

Any adverse reactions present at the last application must be followed up until the event is resolved. The participant is considered to have completed the study EITHER after the completion of the last visit or contact (e.g., phone contact with the site Principal Investigator), OR after the last application of fluoride varnish, whichever is later; OR the participant can no longer comply with the requirements for any further study visits or evaluations.

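### The by-group safety table counts adverse reactions only, so its control row is near zero by definition, and recorded 24 h events of any cause are left out

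*Protocol article*

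**What the plan says.** The *Safety analysis* section fixes both the content and the layout of the safety summary: "The safety data (adverse reactions) – both numbers of subjects and reactions – will be summarised by randomised group and overall using descriptive statistics". It adds: "No formal statistical tests comparing the randomised groups will be pre-specified".

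The *Adverse Reaction (AR)* definition is "Any untoward and unintended response in a subject to an investigational medicinal product which is related to any dose administered to that subject". The section on visits 1 and 2 describes the control contact as a sham, with "applicator brushing teeth with no fluoride varnish on it". At later visits controls receive usual care with an oral check, again without varnish.

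*Detection, recording and reporting of Adverse Events* limits general collection to reactions to the product. It expects any reaction to appear within 24 h of application, and then makes an exception for that window, under which events that parents report are recorded and evaluated "irrespective of whether it constitutes a possible reaction or an unconnected event". The site Principal Investigator is to assess severity and seriousness and to "re-assess their relatedness to the administration of Duraphat varnish". The *Severity* section sets the reporting rule: "Adverse reactions and Serious Adverse Reactions that occur up to 24 h after Fluoride varnish application will be reported".

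**The concern.** A table by randomised group invites the reader to compare its rows. Here one row is settled by the definition before any data arrive. A result of a few children against none would look like a randomised contrast, yet the zero would say nothing about how often such complaints follow a contact without varnish.

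This matters because the reactions quoted from the product information, such as retching, asthma attacks and stomatitis, resemble complaints that can arise in children aged 3 to 5 without varnish. A sham contact is the natural yardstick for them. The events that would supply it are those reported within 24 h regardless of cause. The safety summary leaves these out, and the text does not make clear that they are recorded in controls at all.

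**Working it through.** The article states no safety event rate, so there is no safety figure to reproduce. The check is mainly a reading of the sections against each other.

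1. **What is counted.** *Safety analysis* names adverse reactions as the safety data and tabulates them by group.
2. **What qualifies.** Under *Adverse Reaction (AR)*, the response must be related to a dose given to that child.
3. **Control exposure.** Study contacts in the control arm use no varnish. Two routes to a control count remain: varnish given in error or, loosely, varnish from the child's own dentist, which *Rationale for chosen treatment schedule* allows for up to twice a year. Hence near zero rather than exactly zero.
4. **Result.** The expected control count does not depend on how often complaints follow a sham contact. The difference between the rows therefore cannot estimate an excess after varnish.
5. **What else is recorded.** *Detection, recording and reporting of Adverse Events* has parent-reported events in the 24 h window recorded whatever their cause. *Safety analysis* does not include them.
6. **Whether this covers controls.** The text does not establish it. The window runs from application, the reporting rule in *Severity* refers to varnish application, and *Adverse Event (AE)* defines an event only in a subject given a medicinal product. The use of the word sham for the control contact points the other way, but weakly.

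**What an informative control zero could say.** The *Sample size* section gives a randomised target of 805 per group. If 24 h events of any cause were captured alike in both arms, and none were reported among n control children with at least one contact, the one-sided 95% upper limit for the proportion with a reported event would be 1 − 0.05^(1/n). With n = 805, the most that the target allows, this is 1 − 0.05^(1/805) = 0.0037, or 0.37%. The rule of three agrees: 3/805 = 0.37%. With fewer children contacted the limit is wider. The evaluable target in *Sample size* is not used, because it counts children with two-year caries data and is not a safety denominator. Under the present summary a control zero supports no such limit, since it follows from the definition.

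**The case against.** The strongest reply is that the summary matches a stated and reasoned collection policy. The product is established and its reactions are few, specific and immediate. The *Background* reports 168,000 earlier applications without a reported significant adverse event. On this view, recording 24 h events serves to find possible reactions, and those confirmed then enter the table. No test is planned in that section, no comparative safety claim is made, and a by-group layout would at least show varnish given to a control child in error. An unseen analysis plan could also add a listing of other events.

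Much of this stands. Reactions-only collection across the six-month intervals is defensible and is not challenged here. It remains that the article itself fixes the by-group layout and limits the content to reactions, so the uninformative control row is a stated choice rather than an omitted detail.

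A reader might infer that the sham-arm events are already in hand and merely unused. The documents do not support that, for the reasons in step 6 of the working. In addition, the contact route for parents is the varnish aftercare leaflet, and nothing says that control families receive it.

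A reader might also infer that relatedness will be judged with bias, or that the collection rules contradict themselves. Neither follows: the site Principal Investigator re-assesses relatedness, no attribution rate is given, and the 24 h rule can be read as an exception to the general one.

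**Conclusion.** The point holds as a minor improvement to safety reporting. As written, the by-group table of reactions carries almost no comparative information, because its control row is close to zero by definition. The events that could make the comparison meaningful are left out of the summary, and their recording after sham contacts is not clearly provided for.

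No numerical error is claimed, and no efficacy result, sample size or stated safety threshold changes. The 0.37% limit is only an illustration. It assumes that all 805 control children have at least one contact, that no event is reported, and that capture is the same in both arms. Because capture is by passive parent report, any such limit concerns reported events, not all events.

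The length of the 24 h window is a separate question. So is the sentence in *Statistical analysis plan* that extends Mantel-Haenszel tests to safety event data.

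**What to change.** - In *Detection, recording and reporting of Adverse Events*, state that the same passive 24 h recording rule applies after sham and varnish contacts alike.
- In *Safety analysis*, summarise all events recorded under that rule descriptively by randomised group, among children who had at least one contact, with events judged adverse reactions as a sub-row. The denominator needs stating because *Treatment* keeps in the study children who miss every contact.
- If control events were not captured on the same basis, present the varnish arm only and draw no group comparison. List separately any reaction in a control child given varnish in error.

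The cost is one sentence in each section and one descriptive table, made through the route in *Protocol amendments*. It brings a small amount of extra passive recording in controls, but no extra visit or staff, since the study teams already attend the sham contacts. The downsides are that some unrelated childhood illness will appear in the table and that the counts will describe reported events only.

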#### Visit 3: 6 Month (+/- 3 months) intervention visit to nursery school

In the week prior to the visit parents will be sent the contraindications checklist and covering letter (detailed above). If the parents are aware of any contraindications this checklist will be returned to the nursery school. On arrival at the nursery school the study dental team will ascertain if any checklists have been returned. If no exclusion criteria are identified, the study dental team will again either apply fluoride varnish, or deliver TAU, including a brief oral check, as dictated by the original study arm allocation. As before, children with temporary conditions (e.g., cold sores, abrasions, or systemic illnesses) will not have FV applied, but will remain in the study. Children absent at this or subsequent visits will also continue in the study unless actively withdrawn by a parent or following assessment of any adverse reaction.

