##### Treatment

Starting with the upper right side, the cheek will be retracted with a finger or mirror and the canine and molars dried with a cotton roll. With the cotton roll in place, a small amount of Fluoride Varnish will be applied to the contact points of the canine and molars and to the occlusal surfaces of the molars. The same procedure will be repeated for the upper left quadrant and lower quadrants. The remaining varnish will be applied to the labial surfaces of the canines and incisors. The dental nurse will then complete a check to ensure that all equipment is removed from the mouth and disposed of in line with current procedures.

If the child becomes upset or protests during any part of the procedure, then the procedure will be halted, and only resumed if the child can be reassured and put at ease. If any immediate adverse reaction is suspected, the varnish can be easily removed by toothbrushing, rinsing and spitting. Children who miss one or more of the treatments are still eligible to receive any remaining treatments. Children with an incomplete record of treatments or contacts will be retained in the study, even if all treatments and contacts are missed.

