#### Drug accountability

In order to ensure full traceability, the batch number used for each treatment of every individual participant will be recorded on the Case Report Form. Details will also be recorded on the CRF where there is only partial application.

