### Statistics and data analysis

#### Statistical analysis plan

The study will have a comprehensive Statistical Analysis Plan, which will govern all statistical aspects of the study, and will be authored by the trial statistician and agreed by the Trial Management Group (TMG) before any unblinded data is seen.

Binary endpoints such as evidence of any new decay will be analysed by Mantel-Haenszel Chi-squared tests and odds-ratios, with the attendant 95 % confidence intervals. This type of analysis will also be carried out on safety event data. Changes in d_3_mft will be analysed by Wilcoxon tests, unless these changes are normally distributed and therefore suitable for analysis by Analysis of Covariance. Compliance will be compared with a chi-squared test. The subgroup analyses will be carried out for the primary endpoint using logistic regression with interaction terms between treatment and subgroup. All statistical tests will be two-tailed tests at the 5 % significance level. There should be no concerns regarding multiple testing. All randomised controlled trials examine secondary endpoints to examine consistency of results and to generate hypotheses for further research.

All analyses will follow the intention to treat principle [8, 11]. Study subjects will be analysed in their randomised groups regardless of the treatment actually received. Also, subjects who violate the rules of the study (‘protocol violators’) will be included in all of the analyses, provided that the 2 year endpoint data has been recorded. Ideally an intention to treat analysis would be carried out on all of the randomised subjects, but there is usually some missing primary endpoint data that prevents this. We will also carry out a ‘Worst Case Analysis’ of the Primary Endpoint. In this analysis the missing endpoints will be assumed to be treatment failures, e.g., ‘new decay’.

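### Adverse reactions to varnish are to be summarised by randomised group and overall, so any percentage taken on those groups understates the rate among children given varnish

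*Protocol article*

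**What the plan says.** Under *Safety analysis*, the reaction data, described as "both numbers of subjects and reactions", "will be summarised by randomised group and overall using descriptive statistics". The *Statistical analysis plan* section states the general rule: "All analyses will follow the intention to treat principle". It then adds: "Study subjects will be analysed in their randomised groups regardless of the treatment actually received". The article makes no exception for safety and names no set of treated children.

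Other sections settle who can contribute a reaction:

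- *Adverse Reaction (AR)* defines a reaction as a response related to a dose given to that child. *Detection, recording and reporting of Adverse Events* limits collection to reactions to the study product.
- *Visit 1/visit 2* gives controls a sham application with no varnish on the brush.
- *Treatment* says children with incomplete records "will be retained in the study, even if all treatments and contacts are missed".
- *Visit 3* says children with a temporary condition "will not have FV applied, but will remain in the study".
- *Drug accountability* says "the batch number used for each treatment of every individual participant will be recorded on the Case Report Form", and that partial applications are noted as well.

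**The concern.** Intention to treat protects the efficacy comparison. For a reaction that by definition needs a dose, it places children who could not have the event in the denominator. The error has one direction: it makes the product look safer. The overall column is most affected, because half of its children are controls who receive no study varnish.

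A programme applying varnish needs to know how often a treated child reacts and how often an application provokes a reaction. The article itself reports earlier programme experience per application (168,000 applications, in *Background*). A summary by randomised group cannot be set beside that figure unless the number of applications given is also shown.

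**Working it through.** **Group sizes.** *Sample size* gives 0.41 versus 0.31, two-sided 5%, 90% power, 40% dropout. The usual two-proportion formula without continuity correction gives 483 per group (power 90.05%). Then 483 / (1 − 0.40) = 805 per group and 2 × 805 = 1610 in total. The stated figures reproduce.

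**Dilution.** Let *r* be the proportion reacting among varnish-arm children given at least one study application, and *u* the share of the varnish arm never given one. The documents give neither, so both are assumptions. Assume also that no control receives study varnish by mistake.

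- Reacting children: 805 × (1 − *u*) × *r*
- Rate on the varnish arm as randomised: divide by 805, giving *r*(1 − *u*)
- Rate overall: divide by 1610, giving *r*(1 − *u*)/2

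For *r* = 1.00%:

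| *u* (assumed) | Among treated | Varnish arm as randomised | Overall |
|---|---|---|---|
| 0% | 1.00% | 1.00% | 0.50% |
| 5% | 1.00% | 0.95% | 0.475% |
| 10% | 1.00% | 0.90% | 0.45% |
| 20% | 1.00% | 0.80% | 0.40% |

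The factor of 2 in the last column comes from the allocation ratio alone and needs no assumption about *u*.

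**No reactions observed.** The one-sided 95% upper bound is 1 − 0.05^(1/n).

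- n = 1610 (overall): 0.19%
- n = 805 (varnish arm, all treated): 0.37%
- n = 644 (varnish arm with *u* = 20%, 805 × 0.80): 0.46%

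**How large *u* can be.** A child is never treated only if all four applications are missed, so *u* cannot exceed the share missing the first one. That application follows randomisation as soon as possible and, where logistics allow, at the same visit as the baseline examination (*Study schedule*; *Visit 1/visit 2*). As an illustration, if misses were independent with probability 0.4 at each visit, *u* would be 0.4^4 = 2.6%. Misses will tend to cluster within children, so this is not an estimate. It does show that heavy non-attendance need not mean many untreated children.

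**Per application.** The varnish arm has at most 805 × 4 = 3220 scheduled applications. Absence, same-day exclusion and partial application each reduce the exposure delivered, even in children who count as treated. Only the recorded number of applications gives the right denominator.

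**The case against.** The strongest reply is that *Safety analysis* plans numbers of subjects and reactions and states no percentage or denominator. Table denominators commonly belong to the statistical analysis plan, which is not shown. A total column is also conventional, and readers will know that controls had no varnish.

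Part of this stands. Counts are not diluted, the article does not commit itself to a percentage, and a separate plan may define a treated set. But the article is not silent on grouping: it fixes it as randomised, for all analyses, regardless of treatment received. Any rate built on that text carries the bias, and a treated set defined elsewhere would conflict with it. The *Statistical analysis plan* section also applies odds ratios to safety event data, which need group denominators. That sentence sits badly with the absence of pre-specified tests under *Safety analysis*, which is a separate matter.

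It is also fair that a sham arm gives context for parents' reports in the 24 hours after a visit, which are recorded before relatedness is settled. That is a reason to keep counts by randomised group.

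A reader might infer a much larger loss in the varnish arm, 10% to 40%, by borrowing the 40% dropout from *Sample size*. The documents do not support this. That 40% separates randomised from evaluable children, so it is loss of the 2-year endpoint; a child treated at baseline who later moves away is a dropout but was exposed. Nor does being unfit for varnish at one visit make a child untreated, since later applications remain open.

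**Conclusion.** The point holds as a minor defect in how the safety summary is specified. The direction is certain: percentages or upper bounds on the stated groups understate the reaction rate. In the overall column the understatement is at least a factor of 2, resting only on 1:1 allocation and on controls receiving no study varnish. In the varnish arm it equals the never-treated share, which is unknown and probably small; the 0.95% in place of 1.00% assumes 5%. Data collection and the efficacy analysis are unaffected.

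**What to change.** In *Safety analysis*, state that the safety summary is exempt from the intention-to-treat grouping and is made by treatment received. Report:

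1. children with at least one reaction over children with at least one study application;
2. reactions over study applications given, full and partial, from the case report form records described under *Drug accountability*.

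Keep the counts by randomised group, and show the overall column as counts without a percentage or confidence bound. Align any separate analysis plan with this wording.

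The cost is a sentence or two of text and a small amount of extra table work. No new data are needed.
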